## **3. Experimental Design Type, Principles, and Procedure**

(1) Experimental Design Type: Randomized Controlled Trial

(2) Principles of Experimental Design:

Sample Size Calculation:

The sample size was determined based on our prior pilot investigation. A mean difference in  $VO_{2peak}$  of  $2.6 \text{ ml} \cdot \text{kg}^{-1} \cdot \text{min}^{-1}$ , with a standard deviation (SD) of 3.0 was observed between the moxibustion and control groups. The estimation conducted via the website (<https://sample-size.net/sample-size-means/>). Approximately 29 participants each group are needed to detect a clinically significant difference in outcome measures at a 5% significance level and 90% statistical power. Considering an estimated dropout rate of 15%, the final sample size required will be 35 for each group, resulting in 105 participants. To recruit this number of participants, we anticipate a study period of 9 months based on our pilot study.

Randomization: Stratified Random Allocation

Control: The study includes apparently healthy elderly individuals, with no underlying diseases. Based on recognized principles of effectiveness, safety, and comparability,

sham moxibustion and no intervention are chosen as controls.

-----

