### (2) Statistical Analysis Methods

Summarize the demographic characteristics of each group and baseline variable measurements. The Kolmogorov-Smirnov test will be used for assessing data normality. Continuous data will be represented as the mean  $\pm$  standard deviation for normally

distributed data and median (range) for non-normally distributed data. Paired t-tests or analysis of variance (ANOVA) will be used to assess changes in primary and secondary outcomes before and after intervention. Analysis of variance or Kruskal-Wallis test will be used for pairwise comparison of primary and secondary outcomes among groups. Chi-square or Fisher's exact test will be used for analyzing categorical data. Pearson or Spearman correlation analysis will be used to assess the correlation between variables. Statistical analysis will be conducted using the Windows version of the Social Sciences Statistics Software Package (SPSS) 27.0, with significance set at a two-tailed P-value of  $<0.05$ . Graphical analysis will be performed using GraphPad Prism software (version 9.4.0).

-----

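### The trial is sized for one comparison with an unidentified control, but efficacy can be declared from a three-group test without any moxibustion-versus-sham difference

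*Protocol*

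**What the plan says.** **Sample size (Protocol, Section 3).** The basis is a pilot difference in VO2peak of 2.6 ml/kg/min "with a standard deviation (SD) of 3.0 was observed between the moxibustion and control groups". The target is stated as: "Approximately 29 participants each group are needed to detect a clinically significant difference in outcome measures at a 5% significance level", with 90% power. A 15% dropout allowance brings this to 35 per group and 105 in total. Under the design principles, the same section adds that "sham moxibustion and no intervention are chosen as controls". It does not say which of the two the pilot's control was.

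**Between-group test (Protocol, Section 11(2)).** "Analysis of variance or Kruskal-Wallis test will be used for pairwise comparison of primary and secondary outcomes among groups", "with significance set at a two-tailed P-value of" less than 0.05. No contrast is identified.

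**Efficacy rule (Protocol, Section 8(1)).** Efficacy is judged by whether the main outcome indicators differ statistically. The rule does not say between which groups.

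**Arms (Protocol, Section 5(2)).** Sham uses the same acupoints, session length and 60-session schedule as moxibustion, with a modified device that, according to the Abstract, isolates heat and radiation. The blank group receives no sessions.

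**The concern.** The powered comparison, the test and the efficacy rule are all in the protocol, and they do not describe the same question. The sample size answers whether moxibustion differs from one control. ANOVA and Kruskal-Wallis on three groups answer whether any group differs from any other. The efficacy rule accepts a statistical difference without saying which.

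This matters because the two controls mean different things. Moxibustion versus blank mixes the effect of heat with 60 sessions of contact and expectation. Moxibustion versus sham is the comparison that largely removes those, and it is presumably why the sham device was built. Under the stated rule that comparison does not have to succeed: a significant overall test produced by blank being lower than both other groups would count as efficacy.

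There are two further consequences. The 90% power belongs to a single contrast, so it does not describe a claim against both controls. And if the 2.6 was measured against untreated people, it need not be the difference to expect over sham.

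**Working it through.** **Inputs.** Difference 2.6, SD 3.0, alpha 5%, power 90%, 29 per group, dropout 15%, 35 per group (Section 3); two-sided testing (Section 11(2)); three equal arms (Abstract).

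**1. Reproducing the plan's figure.** Normal approximation: n = 2 × [3.0 × (1.960 + 1.282) / 2.6]² = 27.98, so 28 per group. With the noncentral t distribution, power is 88.96% at 28 and 90.03% at 29, so 29 per group. Dropout: 29 / 0.85 = 34.1, rounded up to 35; 3 × 35 = 105. The stated figures are exactly those of one two-sided two-sample comparison, with no allowance for a second contrast. The protocol does not name a t-test here; it is inferred from the two-group inputs and the exact match.

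**2. What the omnibus test responds to.** The noncentrality is λ = n × Σ(group mean − overall mean)² / SD². Suppose moxibustion equals sham and both exceed blank by 2.6. The means are 2.6, 2.6 and 0, and the overall mean is 1.733. The sum of squares is 0.867² + 0.867² + 1.733² = 4.507, so λ = 29 × 4.507 / 9 = 14.52. With 2 and 84 degrees of freedom, power is 92.8%. A direct moxibustion-sham test is significant in only about 5% of such trials. In roughly 93 − 5 = 88% of them, therefore, the overall test is significant and the moxibustion-sham test is not.

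For comparison, the omnibus power is also 92.8% if sham equals blank, and 83.5% if sham lies halfway (2.6, 1.3, 0). The omnibus test is not generally weak; its result does not identify the contrast.

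**3. Family error when no groups differ** (simulation, 200,000 trials, 29 per arm, each test at 0.05):

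| Reading of Section 11(2) | Chance of any false positive |
|---|---|
| Three pairwise tests, no gate, no adjustment | about 12% |
| Two moxibustion contrasts, no gate, no adjustment | about 9% |
| Pairwise tests only after a significant ANOVA | about 5% |

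**4. Power for more than one contrast**, true difference 2.6 against each control:

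| Requirement | 29 analysed per arm | 35 analysed per arm |
|---|---|---|
| One contrast at 0.05 | 90.0% | 94.7% |
| Each of two at 0.025 | 83.7% | 90.6% |
| Each of three at 0.0167 | 79.4% | 87.6% |
| Beating both controls at 0.05 each | about 83% | about 91% |

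**5. If the pilot control was untreated.** The documents give no difference over sham, so these values are assumptions. Power for moxibustion versus sham at 29 per arm is 90% at 2.6, 70% at 2.0, 47% at 1.5, 37% at 1.3 and 24% at 1.0.

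**The case against.** **A gate may be intended.** Pairwise comparison tied to ANOVA can be read as an overall test followed by post-hoc tests. With exactly three groups, an ANOVA gate with unadjusted pairwise tests holds the family error at about 5% under the global null. With moxibustion equal to sham and blank 2.6 lower, a false moxibustion-sham claim occurs in 5.0%. A reader might infer that the plan exceeds 5% error; the text does not support that, because it does not commit to ungated tests. It does not state the gate either, and a gate would not say which contrast decides efficacy.

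**More than 29 may be analysed.** Section 11(1) carries observations forward so that the number at the endpoint matches the number at the start, which is near 35 per arm. The right-hand power column then applies, and a reader who infers that the trial is underpowered for two contrasts goes too far. The qualification is that carry-forward may dilute the effect, Section 4(5) permits some exclusions, and the sponsor's own 90% is set at 29.

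**The low sham figures are hypothetical.** Nothing in the documents shows that the pilot control was untreated or that the difference over sham is below 2.6. The figures show sensitivity only.

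**Some of this belongs in a SAP.** Post-hoc procedure and alpha allocation are commonly left there, and their absence is not counted here. What stands is what the protocol itself fixes: an omnibus test labelled pairwise, an efficacy rule with no contrast, and a sample size tied to an unidentified control.

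**The power claim may only be loosely worded.** The reference to outcome measures in general follows directly after the VO2peak inputs. It needs tidying but is not a separate power error.

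**Conclusion.** The point stands as a mismatch between the comparison powered, the test named and the rule for judging efficacy. Its main consequence is that, followed as written, the protocol can declare efficacy with no moxibustion-versus-sham difference: about 93% of trials at 29 per arm would have a significant omnibus ANOVA if moxibustion equals sham and both exceed blank by 2.6. That scenario is an illustration built on the protocol's own difference and SD, not a prediction.

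Family error is unspecified rather than shown to be inflated. The 90% is correct for one contrast. The joint power of about 83% or 91% assumes 2.6 against both controls, with 29 analysed or with 35 analysed and an undiluted effect. The total of 105 is not wrong: it stands once one contrast is named and 2.6 is justified for it. Multiplicity across the several primary outcomes is a separate matter and is not included. Wording repairs the defect without changing the design, so it is something the sponsor should fix rather than a fatal flaw.

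**What to change.** **Section 11(2).** Replace the between-group sentence with planned contrasts from one model, tested in fixed sequence at two-sided 0.05: (1) moxibustion versus sham at week 12; (2) moxibustion versus blank, tested only if (1) is significant. Report sham versus blank descriptively.

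**Section 8(1).** Tie the efficacy rule to contrast 1.

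**Section 3.** State which control the pilot used. Restate power as 90% for moxibustion versus sham on VO2peak with 29 analysed per arm if the difference over sham is 2.6, about 83% for both contrasts, and other outcomes not powered.

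A many-to-one procedure such as Dunnett, a rule requiring success against both controls, or an explicit ANOVA gate with a named deciding contrast would also close the gap. The fixed sequence is preferred because it keeps the full 0.05 for the comparison that isolates heat and leaves the sample size at 105. By contrast, holding 90% per contrast with a two-way Bonferroni split would need 35 evaluable per arm, 42 after dropout (35 / 0.85 = 41.2), or 126 in total.

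**Cost.** Wording, a less favourable power statement, and a comparison with blank that is only descriptive if moxibustion does not beat sham. No more participants are needed.

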## **12. Ethical Principles**

(1) Ethical Review: The clinical trial protocol is implemented after approval by the ethics committee. If revisions are made during the trial, it must be re-submitted for approval by the ethics committee before implementation. If significant new information regarding the trial medication is discovered, the informed consent form must be modified in writing, submitted for approval by the ethics committee, and re-obtained from the participants.

This research project undergoes ethical review by the responsible unit's ethics committee before the trial commences. Each participating unit's ethics committee will be informed, and if necessary (such as the occurrence of serious adverse events), meetings should be promptly convened for review, and conclusions communicated to other central ethics committees.

(2) Benefits and Risks: Participants may benefit from this study. These benefits include potential improvements in participants' conditions and the potential development of a new treatment method for other patients with similar conditions. Participants will receive free medical examinations related to the study and registration fees during follow-ups. Participants will receive good medical care during the study.

(3) Recruitment of Participants: Recruitment of participants will be through internal notices posted, interested individuals applying, reading the research synopsis, signing the informed consent form, volunteer physical examinations, screening, and selection of eligible participants through random grouping. Recruitment notices and research synopses are included in the annex and submitted for ethical committee review.

(4) Medical Care and Protection of Participants: Researchers from each participating unit are responsible for the medical care of participants, making relevant medical decisions, and ensuring appropriate treatment if adverse events occur during the trial.

(5) Protection of Participant Privacy: Only research personnel involved in the clinical trial may access the participants' medical records. Data processing will be anonymized, omitting information that could identify individual participants.

(6) Informed Consent Process: Details about the clinical trial, including its purpose, procedures, potential benefits and risks, participants' rights, and obligations, will be explained. Participants will have ample time to consider and have satisfactory answers to their questions before consenting and signing the "Informed Consent Form." Each patient signing the informed consent form should be provided with the doctor's contact number to reach out in case of changes in their condition.

-----

### **13. Summary and Data Preservation**

#### **(1) Summary and Conclusion**

The responsible unit will complete the statistical work of the clinical trial data.

#### **(2) Data Preservation**

Research records (Case Report Forms), informed consent forms, records of moxibustion treatment, etc., will be archived and preserved.

-----

#### **(2) Expected Progress**

Q1 2023: Development of research manuals, study plans, informed consent forms, and related materials.

Q2 2023: Ethical review, recruitment promotion, clinical trial registration.

Q3 2023: Initiate recruitment; draft and publish research proposals.

Q4 2023: Recruitment of participants, completion of preliminary screenings.

Q1 2024: Recruitment of participants, completion of preliminary screenings.

Q2 2024: End recruitment; inclusion and exclusion of participants.

Q3 2024: Stratified random grouping, completion of baseline data collection and recording.

Q4 2024: Commence acupuncture intervention and regular follow-ups.

Q1 2025: End intervention, follow-up on outcome indicators.

Q2 2025: Follow-up phase.

Q3-4 2025: Data analysis, and draft research report.

-----

## 16. Abbreviations

CRF: Cardiorespiratory Fitness

CPET: Cardiopulmonary Exercise Testing

6MWT: 6-Minute Walk Test

VO2peak: Peak Oxygen Uptake

AT: Anaerobic Threshold

SF-36: Short Form-36 Health Survey

QBSQ: the Qi and Blood State Questionnaire
